#### Secondary analysis methods

Fall data will be summarised as number of falls, number of fallers/non-fallers/frequent fallers, fall rate per person year, and time to first fall.

The absolute risk difference between groups will be reported. We will use negative binomial regression to estimate the difference in fall rates between groups. The effect of potential confounders (number of co-morbidities, number of prescribed medication, use of psychotropic medications and cardiovascular health status) will be adjusted for in the regression models. Interactions between falls and frailty (overall and separately for gender and ethnicity) will be examined.

For outcomes with baseline and the post-intervention 24-month follow-up measures only, comparisons of continuous variables between groups will be performed using *t* tests. Where the continuous variables are not normally distributed, non-parametric comparisons using the Wilcoxon rank-sum test will be used. Categorical measures will be compared using the Chi-square test. For outcomes with repeated measures (more than two measurements), generalised estimating equations (GEE) will be used with clustering on participant and an exchangeable correlation matrix.

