## Methods

This trial aims to determine the effectiveness and cost-effectiveness of the SC and/or SAYGO programmes to prevent frailty in pre-frail older adults.

Design: A multi-centre randomised controlled, assessor-blinded, 2 × 2 factorial study.

Setting and characteristics of participants: Community-dwelling older adults aged 75+ (60 + Māori and Pasifika) across four sites in both the main islands of New Zealand (North and South Islands), with no upper age limit. Māori are the indigenous Polynesian people of New Zealand and Pasifika people are migrants from the South Pacific Region who are living in New Zealand. Health inequalities between the Māori/Pasifika and non-Māori/non-Pasifika are evident [26] and Māori/Pasifika people have lower life expectancy than non-Māori/Pasifika [27], so that applying uniform eligibility criteria would exclude Māori and Pasifika older people.

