#### Primary analysis method

A repeated measures generalised linear model will be used to compare the mean number of frailty criteria between randomisation groups over time. The effect of potential confounders (age, number of co-morbidities, number of prescribed medication, cardiovascular health status, energy intake) will be adjusted for in the regression models.

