### Pilot study

A pilot study was carried out between 2014 and 2015 to assess the feasibility of this randomised controlled trial. The pilot study aimed to identify feasibility of the recruitment strategies and the outcome measures, implementation of the SC and SAYGO programmes, and to refine the processes. The pilot study was completed in two of the four sites similar to the main study (Whangarei and Howick) as these locations are ‘new territory’ for research with older adults; the other two have established relationships with local stakeholders. We aimed to recruit 80 older adults with similar eligibility criteria as mentioned above.

We invited 527 age-eligible older adults from four general practices through regular post; 433 (82%) responded to the invitation. Of this, 107 (25%) were interested and eligible; 71/107 were enrolled in the pilot study.

The randomisation procedure was implemented effectively and the utility of the outcome measures is found to be good. The intervention programmes were initiated successfully but the transitioning period to a peer-led class required a longer duration compared to existing community classes. This was attributed to the frailer health status of the sample.

Overall, the pilot study demonstrated that the recruitment strategies were acceptable and additional resources (facilitator time) are required for successful transition to peer-led classes. Three changes were made to the main study: (1) switching from MMSE to MoCA due to MMSE copyright issues; (2) adjusting the eligible age to 60+ (from 75+) for Pasifika as they have similar health profile to Māori; and (3) switching from paper-based questionnaire to the web-based EDC to streamline the data entry process.

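### The falls covariate list omits age, which the primary model includes, so the non-randomised falls-frailty analyses can be partly confounded by age

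*Protocol article*

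**What the plan says.** Three parts of the protocol article bear on this point.

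- **Eligibility (Methods, setting and participants).** The trial enrols "Community-dwelling older adults aged 75+ (60 + Māori and Pasifika) across four sites", with no upper age limit. The reason given for the two floors is inclusion: "applying uniform eligibility criteria would exclude Māori and Pasifika older people". The Pilot study section confirms the lower floor for Pasifika.
- **Primary analysis method.** The covariate list for the frailty model opens with age: "The effect of potential confounders (age, number of co-morbidities". Number of prescribed medications, cardiovascular health status and energy intake follow.
- **Secondary analysis methods.** Fall rates are compared between groups by negative binomial regression, with a separate list: "The effect of potential confounders (number of co-morbidities, number of prescribed medication, use of psychotropic medications and cardiovascular health status) will be adjusted for". The next sentence reads "Interactions between falls and frailty (overall and separately for gender and ethnicity) will be examined". It names no model and no further covariates.

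The Allocation section adds that randomisation is stratified by site and by ethnic group (Māori/Pasifika or not).

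**The concern.** The two covariate lists stand in consecutive subsections. The falls list repeats three of the primary covariates, drops age and energy intake, and adds psychotropic medication. The article writes this list out, so the absence of age is a stated choice and not a detail left to another document. No reason is given.

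For the comparison of randomised groups the omission is harmless. The falls-frailty analyses differ, because frailty is a characteristic of the participant and is not allocated. The article itself treats age as a potential confounder for frailty and says in the Discussion that frailty prevalence increases with age. If fall rates also rise with age, which the article does not quantify, part of any falls-frailty association is age.

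The eligibility rule adds a second element. Everyone aged 60 to 74 in this trial is Māori or Pasifika. Pooling the strata mixes two age ranges. Comparing the association between strata sets a group starting at 60 against a group starting at 75. At stake is the interpretation of an exploratory secondary analysis, not the primary result or the treatment effect on falls.

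**Working it through.** **The documents side by side.**

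| Item | Primary frailty model | Falls regression |
|---|---|---|
| Age | listed | not listed |
| Co-morbidities, prescribed medications, cardiovascular status | listed | listed |
| Energy intake | listed | not listed |
| Psychotropic medication | not listed | listed |

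Difference in age floors: 75 − 60 = 15 years. The article states no figure for an age effect, so there is none to reproduce.

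**Size of the effect, under assumptions.** The documents give no age distribution, ethnic share or age gradient for falls. All of the following are assumed, except the sample of 504 from the Sample size section and the treatment rate ratio of 0.70, which mirrors the 30% reduction stated there:

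- Māori/Pasifika share 10% or 30%. Ages are 60 plus a gamma variable (shape 2, scale 5; mean 70, variance 2 × 5² = 50) in that stratum, and 75 plus a gamma variable (shape 2, scale 3; mean 81, variance 2 × 3² = 18) in the other.
- Odds of frailty rise by a factor of 1.5 per 10 years of age.
- Fall-rate ratio per 10 years of age is 1.10, 1.25 or 1.50.
- The true frailty and ethnic rate ratios are both 1.
- Negative binomial counts with dispersion 1, randomisation stratified by ethnicity, 200 replicates.

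Mean estimated rate ratios:

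| Rate ratio per 10 y | Share | Frailty, no age, ethnicity in model | Frailty, no age, strata pooled | Frailty, age and ethnicity in model | Treatment, without / with age |
|---|---|---|---|---|---|
| 1.10 | 10% | 1.014 | 1.018 | 1.006 | 0.700 / 0.699 |
| 1.10 | 30% | 1.016 | 1.026 | 1.003 | 0.693 / 0.694 |
| 1.25 | 10% | 1.014 | 1.023 | 0.992 | 0.700 / 0.699 |
| 1.25 | 30% | 1.014 | 1.032 | 0.988 | 0.692 / 0.692 |
| 1.50 | 10% | 1.018 | 1.030 | 0.978 | 0.706 / 0.708 |
| 1.50 | 30% | 1.045 | 1.075 | 0.992 | 0.689 / 0.686 |

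Without age, the frailty rate ratio is 1.01 to 1.05 with ethnicity in the model and 1.02 to 1.08 with strata pooled. With age it is 0.98 to 1.01. The age-adjusted values miss 1 by up to 0.022, which indicates the simulation noise, so the smallest shifts are not distinguishable from none. The treatment rate ratio changes by at most 0.003.

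**Comparison between strata.** Within a stratum, the spurious log rate ratio for frailty is approximately (log fall-rate ratio per year) × (log frailty odds ratio per year) × (age variance). At 1.25 per 10 years this is 0.0223 × 0.0405 × 50 = 0.045 in the Māori/Pasifika stratum, a rate ratio of 1.05, and 0.0223 × 0.0405 × 18 = 0.016 in the other, a rate ratio of 1.02. The spurious ratio between the two associations is exp(0.045 − 0.016) = 1.03. At 1.10 and 1.50 per 10 years the same formula gives 1.01 and 1.05. These values follow from the assumed age spreads. They show only that the distortion need not be equal in the two strata.

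**The case against.** The case against making much of this is strong in several respects.

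- **A reader might infer that the treatment effect on falls is biased.** It is not. Allocation is random and stratified by ethnicity, and the simulated treatment estimate is practically the same with and without age.
- **A reader might infer that the plan will present an age artefact as an ethnic difference in fall rates.** No section plans to compare fall rates between ethnic groups. The negative binomial model compares the randomised groups, and ethnicity enters the falls plan only as a subgroup for the falls-frailty analysis. Any figure for an ethnic fall-rate ratio would size a comparison that is not planned.
- **Analysing each ethnic group separately removes the direct effect of the two floors.** This is right. Inside one stratum, the difference in floors does not confound falls with frailty. What remains there is ordinary age confounding, possibly larger where the age range is wider. The floors matter once strata are pooled or compared.
- **The listed covariates may already carry some of the age effect.** Co-morbidity and medication counts probably do so in part. They were not in the simulation, so its shifts are more likely too large than too small on this account.
- **The interaction sentence is brief, and its model may be specified elsewhere.** This is fair for the interaction models, and applying the preceding covariate list to them is an inference. It does not explain why the list that is written out drops a covariate the primary model has.

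**Conclusion.** The point holds in a limited form. The two covariate lists are inconsistent on age, and the falls list is followed by non-randomised analyses for which age is a plausible confounder on the article's own account. A falls-frailty association pooled over ethnic groups, or a comparison of that association between them, can be partly confounded by age.

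The documents do not give the size. Under the assumptions above it is modest: an apparent frailty rate ratio of about 1.01 to 1.08 when the truth is 1, and a similarly small spurious difference between strata. A steeper age gradient or a wider age spread would increase it; adjustment through co-morbidity and medication counts would reduce it. The primary analysis and the randomised falls comparison are unaffected. This is an inexpensive correction to a secondary, exploratory analysis.

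**What to change.** Under Secondary analysis methods, add baseline age as a continuous covariate to the falls list, and state that the falls-frailty models, overall and within gender and ethnic groups, also include it. This matches the primary model. It needs no new data, since age is required for eligibility and already used in the primary analysis, and it costs one model term.

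If falls-frailty results are compared between ethnic strata, state that participants aged 60 to 74 have no comparator outside the Māori/Pasifika stratum, so that adjustment for age over that range relies on extrapolation. A comparison restricted to participants aged 75 and over can be offered as a sensitivity analysis. It should stay optional: it lowers precision, may leave few Māori and Pasifika participants, and reimposes for that comparison the uniform floor that the eligibility rule was written to avoid.

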### Interventions

After participants complete baseline assessments, they are randomly assigned to one of four groups: SC, SAYGO a group strength and balancing exercise, both SC and SAYGO, and social group (control group).

**Senior Chef** is a weekly 3-h session run for 8 weeks by a trained facilitator following set lesson plans. The 3-h session comprises a morning tea (or light snack) prepared by the facilitator, nutrition education, cooking together (hands-on cooking in pairs) using provided utensils and cooking facilities and then sharing the meal cooked that day. The nutrition education covers practical information about sourcing food, menu planning, budgeting and shopping tips and written information is provided to attendees to take home. After completion of the 8-week programme, the group is encouraged to continue to meet as peers as coordinated by the facilitators.

SAYGO (Steady As You Go) is a weekly 1-h session of exercises to strengthen lower limb muscles and to challenge balance for 10 weeks led by a professionally trained facilitator. The exercises are based on the Otago Exercise Programme, one proven to reduce falls and be sustainable [30]. The programme was adapted for group delivery by physiotherapists and found to be effective in improving physical function in those who participate [22]. During the first 6 weeks, potential peer leader(s) are encouraged by the professionally trained facilitator to consider being a peer leader. Other participants in the group are encouraged to support the peer-led class by helping arrange and set up the venue, collect gold coin donations and take attendance. At week 9, peer leaders are invited to take the class in their community and go through a 1-day training. The training includes a physiotherapy-developed manual and covers class safety, fall prevention, specific exercise routines and first aid workshop. There is a CD with all the exercises that peer leaders use to teach their class to maintain fidelity. The peer leaders and class members decide on the venue for the classes, and continue to meet weekly.

Social group (control) is a weekly 1–2-h “seated” (i.e. non-physical in nature) socialising group facilitated in the local community for 10 weeks. Following the 10-week period, participants are encouraged to continue to attend social groups.

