### Sample size

The sample size and power calculations are based on the primary outcome of frailty score. A sample of 504 (126 in each of group) will provide 90% power at a 5% significance level (two sided) to detect a 25% reduction in the mean number of frailty criteria (reduction of 0.43 from 1.68 to 1.25) [49]. With an attrition rate of 20%, the study will enrol 600 eligible older people. This sample size will also provide 80% power at a 5% significance (two sided) to detect a 30% reduction in the rate of falls, reduction of 30% [50] in falls (from 58 to 41% [51]).

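### All four arms are delivered in groups, but no analysis names class as a source of correlation and the power figures carry no design effect

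*Protocol article*

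**What the plan says.** **Delivery (Protocol article, Interventions).** Individuals are allocated to one of four arms. Senior Chef is a facilitated cooking class over 8 weeks, SAYGO a facilitated exercise class over 10 weeks, and the control a facilitated weekly social group over 10 weeks. The fourth arm receives both classes. For SAYGO, the classes go on after the programme: "The peer leaders and class members decide on the venue for the classes, and continue to meet weekly". Senior Chef groups and control participants are encouraged to carry on.

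**Primary model (Primary analysis method).** The article states: "A repeated measures generalised linear model will be used to compare the mean number of frailty criteria between randomisation groups over time". All adjustment variables are participant characteristics. No correlation structure and no class or facilitator term is given.

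**Other models (Secondary analysis methods).** Fall rates are compared by negative binomial regression with participant-level covariates. Outcomes measured only at baseline and 24 months get t, Wilcoxon or chi-square tests. For outcomes measured more than twice, "generalised estimating equations (GEE) will be used with clustering on participant and an exchangeable correlation matrix".

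**Power (Sample size).** "A sample of 504 (126 in each of group) will provide 90% power at a 5% significance level (two sided", for a "reduction of 0.43 from 1.68 to 1.25" in the mean number of criteria. The same sample is said to give "80% power at a 5% significance (two sided) to detect a 30% reduction in the rate of falls". No class size, ICC or design effect appears.

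**The concern.** Members of one class share a facilitator, a venue and each other's company, and outcomes are followed for 24 months. If classes differ in how well they work or hold together, outcomes of classmates are positively correlated. Where classes sit within an arm, that correlation adds to the variance of the arm comparison. Clustering on participant handles repeated visits by one person. It does nothing for correlation between two people in the same class. Individual randomisation and stratification by site do not remove correlation that arises after allocation.

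The consequence would be confidence intervals that are too narrow and p-values that are too small, for the primary outcome, falls and the repeated secondary outcomes, together with a stated power that is too high. The error leans towards declaring an effect.

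**Working it through.** **Inputs.** From Sample size: two-sided 5%, 90% power, 126 per arm, difference 0.43; falls 58% to 41%, described as a 30% reduction. Assumed, because the article does not give them: class size m of 8 to 12 and class-level ICC of 0.01 to 0.05.

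**1. The stated 90%.** No SD is given, so the figure can only be inverted. For 126 v 126:

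SD = 0.43 / [(1.960 + 1.282) × √(2/126)] = 0.43 / (3.2415 × 0.1260) = 1.053.

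For a factorial margin of 252 v 252 the same step gives 0.43 / (3.2415 × 0.0891) = 1.489.

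**2. The stated 80% for falls.** A 30% reduction from 58% is 40.6%. With 126 independent participants per arm:

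power = Φ{[0.174 − 1.960 × √(2 × 0.493 × 0.507/126)] / √[(0.58 × 0.42 + 0.406 × 0.594)/126]} = Φ{(0.174 − 0.1235)/0.0620} = Φ(0.815) = 79.2%.

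With the rounded 41% it is 77.3%. The stated figure is therefore about what one arm against another gives with a design effect of 1.

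**3. Effect of clustering.**

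- Design effect: DE = 1 + (m − 1) × ICC.
- True error of a nominal 5% test: 2 × [1 − Φ(1.960/√DE)].
- Primary power: Φ(3.2415/√DE − 1.960). The value 3.2415 is the standardised difference that gives 90% without clustering, so the missing SD cancels.

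Worked line, m = 12 and ICC = 0.05: DE = 1.55, √DE = 1.245. Error: 1.960/1.245 = 1.574, giving 11.5%. Power: 3.2415/1.245 = 2.604; Φ(0.644) = 74.0%.

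| m | ICC | DE | True SE / model SE | True error | Primary power (90% stated) | Falls power, 58% v 41% (77.3% at DE 1) |
|---|---|---|---|---|---|---|
| 8 | 0.01 | 1.07 | 1.03 | 5.8% | 88.0% | 74.5% |
| 10 | 0.02 | 1.18 | 1.09 | 7.1% | 84.7% | 70.3% |
| 10 | 0.05 | 1.45 | 1.20 | 10.4% | 76.8% | 61.2% |
| 12 | 0.05 | 1.55 | 1.24 | 11.5% | 74.0% | 58.3% |

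**4. If the contrast is the factorial margin.** With SD 1.053 and 252 v 252: 0.43 / (1.053 × 0.0891) = 4.584, so power is Φ(4.584 − 1.960) = 99.6%. At DE 1.55: 4.584/1.245 = 3.682, so power is Φ(1.722), about 96%. For the same design effect, the SE ratio and true error do not change.

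**The case against.** **Silence is not a choice.** Only the GEE sentence fixes a clustering level, and it covers only secondary outcomes with more than two measurements. A reader might infer that the primary model too is set to treat participants as the only cluster. The article does not say so: its correlation structure is unstated, and such detail is often left to a full protocol or SAP. This stands as to the primary and falls models. It does not answer the GEE sentence, or a power statement that carries no design effect.

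**Shared exposure is easily overstated.** It is tempting to write that every class shares a peer leader, cooking partners and travel for 24 months. Peer leaders and continued weekly meetings are described for SAYGO, and cooking in pairs for Senior Chef. Shared rides are encouraged where possible. Stable class membership to 24 months is not documented for any arm. Keeping non-attenders in their arm also dilutes within-class correlation.

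**The error rate is conditional.** If class membership has no effect on outcomes, individual randomisation keeps the test near 5%. Inflation needs real variation between classes. Also, the article does not say whether combined-arm participants sit in the same classes as single-programme participants. If they do, a shared class effect partly cancels in a comparison of those two arms. The comparison with the social group has no such relief.

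**The power loss can be exaggerated.** Enrolling 600 and losing 20% leaves 480, or 120 per arm. A calculation at 120 gives 86% to 72%, but power there is already 88.6% with no clustering (SD 1.053), so that range charges an attrition shortfall to clustering. The table stays at the stated 126.

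**The contrast is not named.** In a 2 × 2 factorial the 90% could refer to margins, with the slack shown above. The falls figure fits arm against arm with no design effect, but that is not proof: 252 v 252 with a design effect of 1.9 would also give 79.4%.

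**Conclusion.** The point holds in conditional form. All four arms are group-delivered, participant is the only clustering level named, no class term is named in the primary or falls models, and no design effect is stated. If outcomes correlate within class and classes sit within arms, standard errors from the plan as written are too small and the stated power is too high.

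The direction is well supported; the size is not. At 126 per arm, for an arm-versus-arm contrast and any SD that gives 90% without clustering, assumed classes of 8 to 12 and an ICC of 0.01 to 0.05 give a true error of 5.8% to 11.5% and power of 88% to 74%. At the low end this is a minor loss. At the high end the nominal 5% test has about twice its stated error. The documents do not say where in that range the trial lies, so they do not support a claim that the trial is underpowered or that its error rate is 10%. Under a factorial margin with SD about 1.05, only the standard-error problem remains.

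**What to change.** 1. **Record class.** Store each participant's class when it is allocated. Attendance sheets already identify it for attenders. Only arm allocation is documented, so the plan also needs a rule for participants never placed in a class.
2. **Model class.** In the primary, falls and GEE analyses, use a random effect for class or a class-robust variance, still respecting repeated visits within a participant. Allow membership of two classes in the combined arm. Add a small-sample correction: at 126 per arm, classes of 12 to 8 mean only about 11 to 16 per arm (126/12 = 10.5; 126/8 = 15.75).
3. **Restate power.** Name the contrast and the SD, and show power over a range of ICC and class size.

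**Cost.** One variable, plus wording in the analysis plan, settled before unblinded analysis. Intervals become somewhat wider and the stated power falls. No extra participants are needed, but this restates power rather than restoring it. Holding 90% for arm-versus-arm contrasts would take 540 analysed at DE 1.07 (126 × 1.07, rounded up to 135, × 4) and 784 at DE 1.55 (196 × 4), against 504.
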